### Objectives

#### Research Hypothesis

We hypothesize that before and after comparisons of voluntary and reflexive saccade performance will show a greater decrease in latency and the number of saccades needed to reach the target, along with a greater increase in saccade amplitude and velocity in Parkinson’s disease participants as compared to participants with no known neurological disorders.

#### Study Objectives

##### Primary objective

To determine whether voluntary saccade training decreases voluntary latency, reflexive latency, and number of saccades needed to reach a target amplitude and increases saccade amplitude in persons with PD compared to persons with no known neurological disorders.

##### Secondary objectives

To determine whether training voluntary saccades affects motor disability in persons with PD. We will also investigate whether training voluntary saccades affects the relationship of the main sequence. Should statistical analysis reveal that these improvements are absent in participants with PD, we propose that saccade performance would be a potential early PD biomarker.

### Trial Design

This trial is designed as a two-arm, pre-post, single center pilot trial with an equal number of participants with PD and participants with no known neurological disorders (control), which will be analyzed using an analysis of variance (ANOVA) with mixed effects.

## Methods: Participants, Interventions, And Outcomes

### Study Setting

All data collection and participant training will be conducted in the Neuroscience of Dance in Health and Disability (NDHD) Laboratory at the University of Illinois at Urbana–Champaign. Access to the laboratory space is limited to the research team and participants, with a partitioned area for saccade training and eye tracking data collection. This protocol has been approved by the local IRB and all NDHD laboratory staff have completed the ethics and best practices training required by the local IRB and the University of Illinois. Due to the small size of this study, Champaign County, Illinois will be sufficient for the recruitment of both study groups. The adult population of Champaign County is approximately 170000 persons and is largely rural. We will attempt to representatively recruit participants according to the ethnicity data provided by the US Census Bureau: 72.4% White, 13.4% Black or African American, 0.4% Native American, 10.9% Asian, 0.1% Native Hawaiian and other Pacific Islander, 2.8% two or more races, and 6.0% Hispanic or Latino^1^.

### Eligibility Criteria

A final decision on inclusion will be made in consultation with the principal investigator once all screening materials are complete (see Figure 2 for a full timeline). During the initial contact interview, the research assistants will read a script describing the study and assessment procedures; if interested, they will be provided via email with the physician release form to be completed by the participant and physician along with the consent form for the participant’s review. Once all questions from the participant regarding the study procedures have been answered by the research team, the consent form is completed, and the physician release form is received via U.S. mail, email, or by hand and reviewed by the principal investigator, a determination will be made whether to proceed with screening using the MoCA and Modified Hoehn & Yahr levels. Only if all inclusion criteria are met, the participant will continue with the study (see Table 2 for eligibility criteria). Research shows that the prevalence of PD in men is 1.5 times greater than in women. Therefore, we expect that ratio will be reflected in our recruitment.

**Table 2 T2:** Eligibility criteria for protocol.

**Inclusion Criteria**
1. To be medically stable with diagnosis of PD by meeting the United Kingdom PD Society Brain Bank Criteria OR- no known neuromuscular disorders for the for the control group.
2. To have a Modified Hoehn & Yahr stage 1–2 (with unilateral involvement only, unilateral and axial involvement, and bilateral involvement without impairment of balance) in the conventionally defined OFF medication state.
3. To have medical clearance form from their physician for participation in the study.
4. To be in a stable regimen of PD medication 30 days prior to the initiation of the study and until the completion of the study.
5. To be willing and able to provide informed consent.
6. To be of age 40 and up.
7. Must have a caregiver/family member present for OFF-state assessment sessions.
**Exclusion Criteria**
1. Presence of dementia based on The Montreal Cognitive Assessment (MOCA) – score of less than 25.
2. Diagnosis of comorbid neurological disorder such as epilepsy.
3. History of neurological injury such as stroke.
4. History of brain surgery such as deep brain stimulation.
5. Concurrent severe medical illness which in the opinion of the research team will preclude participation in the study (such illnesses may include but not limited to severe or uncontrolled cardiovascular disease, hypertension, pulmonary disease, or diabetes).
6. Inability to attend and participate in at least seven of the training sessions.
7. Uncorrected vision, history of retinal disease (e.g., macular degeneration), presence of optic neuropathy due to glaucoma or ischemic optic neuropathy, pseudoexfoliation syndrome, ocular surgery, ocular trauma, visually significant cataract, orbital myositis, blindness or refractive errors outside –5 to +3 D.
8. Indication by the participant s neurologist in the medical release form that testing the participant in the OFF-medication state would put PD participants at significant risk for medical complications.

### Voluntary Saccade Training Intervention

#### Equipment

Training and testing will be performed using the SR EyeLink II eye tracking system (SR Research). The EyeLink II system for assessments and training has two cameras on a head mount located directly below eye level. The pupil is tracked by a device that captures infrared light reflected off the lens and cornea of the eyes. The lens, cornea, and other parts of the eye absorb a small amount of energy from infrared light, but the energy is less than 18% of the Maximum Permissible Exposure level as certified by the American Standards Institute (ANSI Z 136.1-1973). The EyeLink II system will be mounted to the participant’s head using the adjustable straps, such that the head camera bar will be parallel to the display screen, on which four infrared emitters will be placed in a rectangle. The participant will be then positioned, using a chin rest support, so that the participant’s resting focus point will be at the center fixation target display on the screen in the middle of the rectangle of emitters. The experimenter will position the eye tracker on the participant’s head so that the participant can see targets displayed at the amplitude of interest. The chin rest also serves to isolate eye-movements from head movements during eye tracking and maintain a set distance from the display screen. A Sharp Aquos 178.5 cm by 100 cm television will be used as the display for the participant (Sharp Corporation, Sakai-ku, Sakai, Japan). This screen mirrors the computer display visible to the experimenter during training and testing sessions. A second host computer runs the SR Research data capture and processing during sessions. The host computer also displays pupil position and the view of the left and right eye cameras in real time. After adjusting the eye cameras and pupil threshold to track the pupils moving in the eight cardinal and intercardinal directions, the cameras will be then calibrated using the SR Research program. The experimenter will then perform a validation of the camera calibration prior to beginning a training or testing block.

#### Training

Over the course of the four-week intervention period, participants will undergo eight training sessions of 30 min each. During each training session, three target amplitudes will be trained on the six target amplitudes: 10°, 20°, 30°, 40°, 45°, and 50°. Each amplitude will be trained in two different training sessions over the course of the intervention period. This follows an intercalated training schedule of progressive and regressing load design (see Table 3). For each amplitude, the participants perform saccades to each of the eight cardinal and intercardinal directions. Each direction will be indicated five times for a total of 40 trials per amplitude per session. Participants will place their head on a chin rest 40 cm away from the screen in order to isolate the movement of the eyes. Training will involve a visual display designed to initiate only voluntary saccades. Training will begin with a warm-up for the eyes in order to reduce the possibility of injury. Participants will foveate on a central fixation starting point and wait for an instructional arrow that points to one of eight visual targets arranged in eight cardinal points in the perimeter of a circle.

**Table 3 T3:** Training schedule of amplitudes. On both sessions of each week, the same three amplitudes will be trained.

Week	Amplitudes Trained
1	10°, 20°, 30°
2	10°, 20°, 40°
3	20°, 30°, 45°
4	20°, 40°, 50°

Every trial consists of a fixation period, target circle presentation period, direction indication period, and resetting period (see Figure 1). During the fixation period the participant is instructed to focus on the center of a circular fixation bulls-eye target. Next, in the target circle presentation period, a circle of targets in each of the eight directions is presented around the central fixation target. The central fixation target is then replaced by an arrow indicating which direction to look in and fixate on the target there located. After the fixation is recorded at the indicated target, the resetting period follows with the presentation of the sole central fixation target. Due to the nature of mass-practice of eye movements, there is an inherent risk of eye fatigue or strain in participants. However, participants in this study will be instructed to rest at the first sign of any eye pain or fatigue, to minimize the risk and influence of strain or fatigue on the outcomes of the experiment.

**Figure 1 F1:**
[figure not shown]
Example training/testing trial display sequence. **(A)** Central fixation target, **(B)** 20° target circle, **(C)** northern direction indication arrow, and (D) blank reset screen. All images presented in 800 × 600 resolution on screen.

**Figure 2 F2:**
[figure not shown]
Participant flow timeline.

**Figure 3 F3:**
[figure not shown]
Example reflexive testing trial display sequence. **(A)** Central fixation target, **(B)** 20° northeast target, and **(C)** blank reset screen. All images presented in 800 **×** 600 resolution on screen.

Participants who are unable to complete seven of the eight training sessions due to fatigue or other events related to the intervention will be omitted from the study and receive prorated compensation. The intervention is designed to minimize fatigue by providing rest breaks regularly and as the participant indicates a need for rest. During both the training and testing sessions, eye tracking data will be collected by the SR Eyelink II system and stored. While only testing session data will be analyzed to determine the effects of the intervention, training session data can be used to check that training sessions will be completed per the protocol instructions. This check data includes the number of trials per direction per amplitude, amplitudes trained, and collection dates for each session.

### Modifications

In the unlikely case of an unexpected event, the research team, in consultation with the participant’s physician, will make the decision to modify or terminate the trial. As this is a pilot trial, there will be no adjustment to sample size in the course of the study.

### Concomitant Care

(1) Involvement in other interventional studies will not be permitted for participants in either group.(2) Participants will continue their physician prescribed treatment during their participation.

### Outcomes

#### Primary Outcome Measures

The primary outcomes of this study are four measures of voluntary and reflexive saccade performance: (1) the normalized amplitude calculated as the amplitude of the saccade divided by the target eccentricity, (2) the mean normalized saccadic velocity calculated as the mean normalized amplitude divided by saccade duration, (3) saccadic latency calculated as the time from the presentation of the directional cue to the saccade onset. The saccade onset is calculated as the time between the presentation of the directional arrow and the first eye movement crossing the velocity threshold of 30°/s and the acceleration threshold of 8000°/s^2^ specified by the EyeLink^^®^^ II User Manual (Jainta et al., 2011). The fourth outcome is the number of saccades needed to reach the target. The first three outcomes are only calculated on the first saccade toward the target.

#### Secondary Outcome Measures

One secondary outcome for this study is Movement Disorder Society-sponsored new version of the Unified Parkinson’s Disease Rating Scale (MDS-UPDRS). The MDS-UPDRS assesses motor examination and complications, motor aspects of daily living, and non-motor aspects of daily living using a combination of questionnaire and task performance assessment (Goetz et al., 2008; Martinez-Martin et al., 2013). The MDS-UPDRS will only be assessed in participants with PD, as participants with no known neurological disorders should not present disability measurable with these instruments. Additionally, the peak saccadic velocity, duration, and amplitude will be analyzed as a measure of changes to the main sequence (Bahill et al., 1975).

Primary outcomes will be assessed by a member of the NDHD laboratory staff blinded to secondary outcome assessment, which will be performed on a separate day (see Table 5 for investigator team timeline). Secondary outcome assessors will be blinded to primary outcomes and will not be involved in training sessions. Changes after the four-week intervention from the initial value of each primary and secondary outcome measure will be analyzed using an ANOVA of mixed effects.

### Participant Timeline

Table 4 contains a full timeline of participant involvement.

**Table 4 T4:** Timeline of participant involvement.

	Study Period					
	Enrolment	Allocation	Post-allocation			
Timepoint	*Week* –*1*	*Week 0*	*Week 1*	*Week 2*	*Week 3*	*Week 4*
**Enrolment:**						
Eligibility screen	X					
Informed consent	X					
Medical release	X					
Allocation		X				
**Intervention:**						
Parkinson’s group			X	X	X	X
Healthy group			X	X	X	X
**Assessments:**						
Clinical Screening		X				
Saccades			X			X
Clinical			X			X

#### Sample Size

There will be two groups with the same treatment: (1) a control group of participants with no known neurological disorders and (2) a test group comprised of participants with PD that have H&Y levels 1–2. In the absence of existing data in the literature to estimate the required same sample size for a protocol of this nature, the estimation is based on the number of eyes tested and trained in other eye movement studies and a 10% attrition rate seen in other studies performed by the authors (Hall et al., 2010; Knox and Wolohan, 2015; Ivanov et al., 2016; Heath et al., 2017).

### Recruitment

Persons with PD (*n* = 22) and neurologically healthy persons (*n* = 22), between the ages of 40 and 65 years will be recruited. Participants will be recruited from the local community through posted flyers, advertisements in UIUC s newsletter E-WEEK, and support groups (in a 60-mile radius around the UIUC campus).

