**Descriptive Title:** A two-arm, pre/post-protocol to compare the effects of a four-week voluntary saccade training intervention in persons with Parkinson’s disease and healthy adults aged forty years or older.

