## Introduction

### Voluntary Saccade Function Impairment in Parkinson’s and Healthy Aging Adults

Visual function is a major area of decline in Parkinson’s disease (PD) progression and healthy aging adults (Terao et al., 2011; Dowiasch et al., 2015). One element of visual function that has been correlated with PD progression and neurologically healthy aging by a number of studies is saccade behavior (Terao et al., 2011; Dowiasch et al., 2015; Seferlis et al., 2015; Noiret et al., 2017). Saccades are the ballistic eye movements that allow the high acuity fovea of the retina to quickly orient toward salient elements of the visual environment. Persons with PD exhibit lower saccade amplitude, higher saccadic latencies, and longer durations to achieve targets (Mosimann et al., 2005; Terao et al., 2011). Deficits in voluntary saccade control contribute to mobility impairments related to turning during navigation (Ambati et al., 2016; Nemanich and Earhart, 2016). It has been noted that turning during navigation in persons with PD increases instability and risk of falling (Stack and Ashburn, 1999). Voluntary saccade function deficits are also present to a lesser extent in neurologically healthy aging adults (Chen and Machado, 2016; Fernandez-Ruiz et al., 2017).

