## Methods: Data Collection, Management, And Analysis

### Saccade Function Testing

During the week prior to and the week following the intervention period, participants will be tested for both voluntary and reflexive saccade performance (see Table 6 for summary of saccade testing). Voluntary saccade testing will involve the same task as the training sessions, in the 10°, 20°, and 30° amplitudes only. In the reflexive saccade testing session, the same amplitudes will be tested following the reflexive testing protocol. As in the voluntary saccade testing, each amplitude will be tested for the eight cardinal and intercardinal directions. Five trials will be performed per direction, resulting in 40 trials per amplitude in a testing session. The structure of each trial consisted of the initial fixation period, followed by the simultaneous disappearance of the central fixation target and appearance of the reflexive target, and finally the resetting period. Unlike in the voluntary saccade trials, there is no presentation of the circle of targets prior to the appearance of the reflexive target and no arrow to indicate the direction of movement to be performed (see Figure 3). Assessments will begin with a warm-up for the eyes in order to minimize the risk of injury. Participants with no known neurological disorders (see Supplementary Material Data Sheet 2 sample physician release form) will complete only the eye-tracking related assessments. There will be one pre-training assessment and one post-training assessment, totaling two assessment periods for the control group protocol. Each assessment period should last no longer than 1.5 h including rest periods.

**Table 5 T5:** Investigator team activity timeline.

			Approximate	Prestudy	Basline/			Intervention
	PD Only		time to	screening/	Intervention	Intervention	Intervention	week 4/
Activity/assessment	(Yes/	No)	Staff member	complete	(min)	consent	week 1	week 2	week 3	conclusion
Prescreening consent		Study coordinator	5	X				
Screening checklist		Study coordinator	10	X				
Consent form		Study coordinator	45	X				
Medical release and relevant medical history	Yes	Potential participant’s neurologist	30	X				
Hoehn and Yahr scale	Yes	Clinical assessors	30		X			
Montreal Cognitive Assessment	Yes	Clinical assessors	30		X			
Unified Parkinson’s Disease Rating Scale	Yes	Clinical assessors	30		X			
Voluntary saccade assessment		Staff member	45		X			
Reflexive saccade assessment		Staff member	45		X			

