## Ethics and Dissemination

### Research Ethics Approval

All methods have been approved by the local IRB committee (see Table 8 for a full IRB revision history as of the publication of this article). All subjects will provide written informed consent (see Supplemental Materials Data Sheet 1 sample informed consent for informed consent form) in accordance with the Declaration of Helsinki. This protocol has been designed in accordance with SPIRIT guidelines for clinical trial protocols (see Table 9 for a summary of SPIRIT-required trial registration information).

**Table 8 T8:** IRB protocol revision chronology.

**Original Submission**	July 2, 2015	
Approval date	January 15, 2016	
Amendment 01	February 16, 2016	Update of research team list.
Amendment 02	October 3, 2016	Change in research location to Freer Hall room 250.
Amendment 03	July 31, 2017	Addition of testing in the off-medication state for participants with PD.
Amendment 04	April 9, 2018	Update of research team list.
Amendment 05	July 19, 2018	Medical release form specific to healthy controls added.

**Table 9 T9:** Trial registration data.

Primary registry and trial identifying number: 17784042
Date of registration in primary registry: July 25, 2018
Secondary identifying numbers: N/A
Source(s) of monetary or material support: Unfunded
Primary sponsor: University of Illinois at Urbana–Champaign
Secondary sponsor(s): None
Contact for public queries: [name], Ph.D., MA [contact]
Contact for scientific queries: [name], Ph.D., MA University of Illinois at Urbana–Champaign
Public title: Voluntary saccade training in persons with Parkinson’s disease and healthy adults
Scientific title: Voluntary saccade training in persons with Parkinson’s disease and healthy adults – two-arm, pre/post-trial
Countries of recruitment: United States of America
Health condition(s) or problem(s) studied: Parkinson’s disease, voluntary saccades, reflexive saccades
Intervention: Voluntary saccade training
Key inclusion and exclusion criteria: Ages eligible for study: ≥40 years; Sexes eligible for study: both; Accepts healthy volunteers: yes

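### Eligibility rules conflict on the age limit and on who takes the MoCA, and no rule balances the non-randomised controls on age or sex

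*Protocol article*

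**What the plan says.** **Age.** The Abstract and Recruitment give the same range for PD and healthy participants: people "between the ages of 40 and 65 years will be recruited". Inclusion criterion 6 in Table 2 reads "To be of age 40 and up". The descriptive title refers to "healthy adults aged forty years or older". Table 9 has "Ages eligible for study: ≥40 years" and repeats the open-ended minimum in the inclusion list of each group.

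**Sex.** Eligibility Criteria notes that PD is 1.5 times as prevalent in men, then adds: "Therefore, we expect that ratio will be reflected in our recruitment". It does not say whether this covers controls.

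**MoCA.** The first exclusion in Table 2 begins "Presence of dementia based on The Montreal Cognitive Assessment (MOCA" and sets the cut-off at a score under 25. Table 9 splits the inclusion criteria by group but gives one exclusion list for both, with the MoCA in it. Eligibility Criteria describes MoCA screening without limiting it to PD. Table 5 marks the MoCA row as PD only, and Saccade Function Testing says that controls "will complete only the eye-tracking related assessments".

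**Comparability.** Table 9 states that there is no randomisation. Trial Design requires equal group sizes. No other balancing rule appears. The Introduction says: "Voluntary saccade function deficits are also present to a lesser extent in neurologically healthy aging adults".

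**The concern.** The age conflict decides who may enter. A 70-year-old qualifies under Table 2 and Table 9 and falls outside the Recruitment section. Table 9 lists the trial as recruiting, so staff are working under two rules.

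The MoCA conflict decides whether one exclusion operates in half the sample. The voluntary task requires the participant to interpret an arrow cue, so unequal cognitive screening could matter for the outcome.

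The between-group comparison carries the trial's conclusions in both directions. Explanation for Choice of Comparators treats a larger PD response as evidence of improvement and a missing response as possibly characteristic of PD. The Discussion builds a diagnostic biomarker on the latter. With groups defined by disease, a difference in age, sex or cognition that alters trainability could produce either result.

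**Working it through.** **1. Age statements side by side**

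| Place | Lower limit | Upper limit |
|---|---|---|
| Abstract | 40 | 65 |
| Recruitment | 40 | 65 |
| Descriptive title | 40 | none |
| Table 2, inclusion 6 | 40 | none |
| Table 9, age row and both inclusion lists | 40 | none |

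Each place applies its range to both groups or does not separate them. The conflict concerns the study population and does not by itself make the groups unequal.

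**2. MoCA statements side by side**

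- For both groups: the exclusion list in Table 2, the common exclusion list in Table 9, and the screening text in Eligibility Criteria. In the exclusion lists only the OFF-state item names PD participants, so a restriction is written where one is meant.
- For PD only: the MoCA row of Table 5.
- Ambiguous: the eye-tracking-only sentence, which sits in the section on pre- and post-training testing.

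Under Table 5 as scheduled, no MoCA score exists for a control, so the exclusion cannot be applied to that group.

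**3. Sex.** A ratio of 1.5 to 1 among 22 PD participants gives 22 × 1.5/2.5 = 13.2 men. The document fixes no corresponding number for controls.

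**4. When an imbalance biases the result.** The contrast is the difference between groups in pre-post change. If age shifts the pre and post values equally, the shift cancels. If the change itself varies with age by *b* SD (of the change score) per year and mean ages differ by *d* years, then

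bias = *b* × *d*.

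**5. Size on assumed inputs.** The protocol gives no SD, effect size or age slope. Assumed: *d* = 5 to 15 years and *b* = 0.01 to 0.03 SD per year. With 22 per group and the stated 10% attrition, 22 × 0.90 = 19.8, taken as 20 completers per group.

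SE = √(2/20) = 0.316 SD. Rejection rate = P(|Z + bias/SE| > 1.96).

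| *d* (years) | *b* (SD/year) | Bias (SD) | Rejection of a true null |
|---|---|---|---|
| 5 | 0.01 | 0.05 | 5.3% |
| 10 | 0.02 | 0.20 | 9.7% |
| 15 | 0.03 | 0.45 | 29.6% |

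A second parametrisation uses bias = correlation of age with change × (age difference/SD of age) and a t test with 20 per group. With differences of 5 to 10 years, age SD 8 to 10 and correlation 0.1 to 0.3, it gives 5.3% to 21%. A correlation of 0.5 takes the top to 49%. The upper end is therefore set by the assumption.

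For scale, the difference detectable with 80% power is (1.96 + 0.84) × 0.316 = 0.89 SD. The middle bias of 0.20 SD is 0.20/0.89 = 22% of that.

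**The case against.** Several points on the other side stand.

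- A reader might infer that age confounds the comparison outright, or that an age effect could not be told from a PD effect. The protocol's statements concern the level of saccade performance, and a constant effect on level cancels in pre-post change. Bias needs effect modification, which no section asserts. No section links sex to saccades at all.
- A reader might infer that the mixed-effects ANOVA omits age and sex. Statistical Methods lists outcome variables and does not set out the fixed effects. Covariates are commonly left to an analysis plan, so silence does not show that they are excluded.
- A reader might infer that controls are never screened for cognition. The eye-tracking-only sentence need not reach back to screening. Table 5 is also incomplete for controls: its only medical-release row is marked PD only, although Table 9 requires clearance from controls and Amendment 05 added a form for them. Controls must also be free of comorbid neurological disorder and neurological injury.
- The expected sex ratio is said of recruitment generally, so it may be meant for both groups.
- The trial calls itself a pilot, and at the low end of the assumed range the error rate is essentially nominal.

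What these points do not remove is the two contradictions and the absence of any balancing rule. The generic screening text does not settle the MoCA question either, because the same sentence names Hoehn & Yahr staging, which has no use in controls. Who is recruited as a control is a design decision, and later modelling cannot supply overlap in age that recruitment did not create.

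**Conclusion.** Two contradictions are established from the text alone: the upper age limit, and whether the MoCA exclusion applies to controls. The lack of any stated age or sex balancing in a non-randomised comparison is a real but moderate design weakness.

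Its effect on the group-by-time contrast depends on whether age, sex or cognition modifies the response to training, which the document does not quantify. The main illustration runs from about 5% to 30% false positives, with about 10% in the middle case. It rests wholly on assumed age gaps and slopes and on 20 completers per group. The 30% figure pairs both extremes, and a 15-year gap in means would be hard to reach if the 25-year span from 40 to 65 applies. These figures show what is possible and are not evidence that bias will occur. Severity is below must-fix.

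**What to change.** 1. State one age range in the Abstract, descriptive title, Table 2, Recruitment and Table 9.
2. Reconcile Table 5 with Eligibility Criteria, Table 2 and Table 9, so that the same MoCA criterion applies to controls still to be screened. Make clear whether the eye-tracking-only sentence covers screening.
3. Frequency-match the remaining controls to the PD group on age and sex, and say whether the expected sex ratio applies to both groups.
4. Adjust the group-by-time contrast for age and its interaction with time, and for sex likewise if the sample allows, at least as a pre-specified sensitivity analysis.

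**Cost.** Item 1 is wording. Item 2 takes at most 22 × 30 min = 11 assessor hours, and only if all 22 controls were still to be screened. Item 3 slows control recruitment somewhat. Enrolment began in March 2016 and the number of controls outstanding is not given, so matching may have little left to act on; controls already enrolled cannot be matched retrospectively. Item 4 costs two model terms for age and four with sex, from about 40 participants. Age has to be known to check eligibility, and sex is presumably recorded.
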